#### Effect evaluation

We will use an “intention to treat” approach to compare the effects of the different therapy conditions on both primary and all secondary outcomes. Data analysis will be performed using the statistics software SPSS 22 (IBM Corporation, New York, NY) for ODI at 6 months and all secondary outcomes at 6 months. The intervention group will be tested against the control group using two-sample *t*-test and Wilcoxon rank sum test depending on the data level of the outcomes. Interrelationship among the variables will be analysed using a multiple regression model with the ODI as outcome and the secondary outcomes as explanatory variables. In addition, possible mediations and interactions will be investigated. Since this trial will include repeated measures at different time-points, we will use a linear mixed model with random intercept [65].

To test the physical activity level between the groups at 3 and 6 months, we will use a two-sample *t*-test.

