### Recruitment and randomization

Trial participants will be recruited from two private spine clinics and one university hospital. Patients will be clinically examined by an orthopaedic surgeon, who will make a medical diagnosis based on the clinical and radiological findings. Patients who are diagnosed with DDD will be informed that lumbar fusion surgery is a treatment option. When a patient agrees to undergo surgery and is placed on the waiting list, the hospital and the spine clinics coordinators will inform the physiotherapist (*PT-prepare*) who will deliver the trial intervention. Then the *PT-prepare* will call the patient to inform him/her of the trial and invite him/her to participate.

Patients interested in participating will meet with an independent observer at baseline, 8–12 weeks before surgery at one of the private spine clinics. The independent observer will once again provide the patient with information about the trial. If the patient agrees to participate, he/she will sign an informed consent form provided by the independent observer. The independent observer will then guide the participant through the functional capacity testing and provide him/her with the patient-reported outcome measures and the accelerometer. After this, the independent observer will give the participant a sealed envelope containing the group allocation.

The participant will be randomly allocated to Group A or Group B using a computerised random list with no restrictions, arranged by an independent statistician. The project leader – who will not take part in the intervention and outcome assessments – will be responsible for arranging sequentially numbered, opaque, sealed envelopes. To conceal the group allocation, the participant will not open this envelope in the presence of the independent observer. The allocation list will be stored in a locked fire-proof cupboard at the university laboratory, in accordance with the principles of the ethical approval.

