### Outcome measures

#### Primary outcome measure

Disability will be measured using the revised version (version 2.0) of the Oswestry Disability Index (ODI). In the ODI, patients rate their perceived disability on 10 items relating to pain intensity, personal care, lifting, walking, sitting, standing, sleeping, sex life, social life and traveling Each item is scored from 0–5, with 0 indicating the least amount of disability and 5 the most severe disability. The scores are summed to generate a total score ranging from 0 to 100, with 0 indicating no disability. The English version of the ODI shows high internal consistency [42] and test–retest reliability [43], as well as adequate content validity and responsiveness [44] for patients with CLBP.

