### Data collection

Data collection for the patient-reported outcome measures will take place at baseline (8–12 weeks before surgery), at 1 week before surgery; and at 3 weeks, 8 weeks, 3 months, 6 months, 1 year, 2 years and 5 years after surgery. Each participant will have a special numeric code, and all data will be stored in a fireproof cupboard and on a password-protected computer at one of the spine clinics. Double data entry and missing data in the questionnaires will be checked as soon as the participant has done the follow-up by an independent trial coordinator. Figure 4 presents details of the follow-up sessions.

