### Analyses

#### Sample size

The number of participants (*n* = 110) was determined based on a power analysis (80 % power, alpha = 0.05), with disability measured with ODI as the primary outcome. We determined that we required a sample size of 55 patients in each group to show a statistically significant between-group difference of at least 8 points in the ODI with a standard deviation of 15 based on earlier studies [57, 63]. The difference of 8 points on the ODI was based on the previously reported minimal clinically important difference within the range of 5.2–16.3 where 10 points are mostly used for the ODI in a similar population [57, 64].

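### The 6-month ODI comparison is an unadjusted two-sample test: it is valid and has about the planned power, but it gives up precision that the baseline ODI would supply at no cost

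*Protocol article*

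**What the plan says.** The Effect evaluation section of the protocol article places the analysis at one time point, "for ODI at 6 months and all secondary outcomes at 6 months". It then fixes the method: "The intervention group will be tested against the control group using two-sample" t-test or Wilcoxon rank sum test, according to the data level of the outcome. No covariate, change score or analysis of covariance is named for this comparison.

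The same paragraph names two other models. One is a multiple regression with ODI as outcome and the secondary outcomes as explanatory variables, which is not a treatment comparison adjusted for baseline. The other is for the repeated measures: "we will use a linear mixed model with random intercept". Its role relative to the two-sample test is not stated, nor is the way baseline enters it.

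Two other sections matter here. Under Data collection, "Data collection for the patient-reported outcome measures will take place at baseline", 8 to 12 weeks before surgery. Under Recruitment and randomization, the observer runs the functional tests, hands out the questionnaires and the accelerometer, and only then gives the participant the sealed envelope. The allocation itself is made "using a computerised random list with no restrictions", so neither blocking nor stratification balances baseline ODI.

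**The concern.** A two-sample test on the 6-month score treats all variation between patients as noise. The part of that variation already visible in the baseline score can be removed, because baseline ODI is available and, on the natural reading of the visit sequence, is recorded before the participant learns the allocation.

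Two things are at stake. The confidence interval for the primary effect is wider than the data require. And with unrestricted randomisation of 110 patients, a chance difference in baseline ODI passes in part into the 6-month difference, and the named test has no means of removing it.

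The paragraph also leaves open whether the two-sample test or the mixed model answers the 6-month ODI question. Naming one adjusted analysis as primary settles both points.

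**Working it through.** **Inputs from the Sample size section.** A "between-group difference of at least 8 points in the ODI", SD 15, 55 per group, 80% power, alpha 0.05. Sidedness is not stated. Two-sided is inferred, because a one-sided calculation gives 44 per group.

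**Inputs not in the article, so assumed.** The correlation r between baseline and 6-month ODI (range 0.2 to 0.6), and a baseline SD of 15 for the imbalance calculation only.

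**Step 1: reproduce the plan's own figure.**
- n per group = 2 × (1.960 + 0.842)² × 15² / 8² ≈ 55.2, which is 56 when rounded up. The t-based solution is 56.2, or 57 when rounded up. The stated 55 agrees with the unadjusted comparison to within 2 patients.
- Power at 55 per group is 79.9% by the normal approximation and 79.2% by the noncentral t. The SD of 15 was therefore used without any reduction for baseline.

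**Step 2: precision with baseline adjustment.** The residual SD is 15 × √(1 − r²). The standard error falls by the fraction 1 − √(1 − r²). The 95% half-width is 1.96 × residual SD × √(2/55). Power is by the noncentral t at 55 per group.

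| r (assumed) | Residual SD | Fall in SE | 95% half-width | Power |
|---|---|---|---|---|
| 0 (as planned) | 15.00 | none | 5.61 | 79.2% |
| 0.2 | 14.70 | 2% | 5.49 | 80.8% |
| 0.3 | 14.31 | 5% | 5.35 | 82.8% |
| 0.4 | 13.75 | 8% | 5.14 | 85.6% |
| 0.5 | 12.99 | 13% | 4.86 | 89.3% |
| 0.6 | 12.00 | 20% | 4.49 | 93.4% |

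These are figures for an analysis of covariance with complete 6-month data. A baseline-adjusted mixed model should give a similar gain at that visit.

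**Step 3: chance imbalance.** With a baseline SD of 15, the standard error of the baseline difference is 15 × √(2/55) = 2.86 points, so 95% of chance baseline differences lie within 1.96 × 2.86 = 5.6 points. Taking the 6-month SD as 15 too, only r times the baseline difference carries over into the 6-month comparison:
- r = 0.3: 0.3 × 5.6 ≈ 1.7 points at the 95% limit (0.9 for an imbalance of one standard error).
- r = 0.5: 0.5 × 5.6 = 2.8 points at the 95% limit (1.4 for an imbalance of one standard error).

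The target difference is 8 points.

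**Step 4: illustration with loss to follow-up.** With an assumed 10% loss in each arm, power is about 75% unadjusted, 79% at r = 0.3 and 86% at r = 0.5.

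**The case against.** The strongest reply is that nothing is wrong with the test. Under randomisation it keeps its type I error rate and is unbiased on average, and the sample size was calculated for exactly this comparison. The power forgone is power above the planned 80%. That stands, and it sets the weight of the point.

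The second reply is that the size depends on a correlation the article does not give. Fusion surgery lies between the two measurements, so a low value cannot be excluded; at 0.2 the gain in power is under 2 percentage points. That also stands, and it is why a range is shown.

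Some stronger readings are tempting, but the document does not support them:
- **The chance baseline difference of 5.6 points could swamp a target of 8.** The two are not comparable. Only r times the baseline difference reaches the 6-month estimate, and this variation is already counted in the unadjusted standard error.
- **The mixed model also ignores baseline.** The article is silent on that model's covariates. An article may leave such detail to a fuller plan.
- **The t-test breaks the intention-to-treat commitment because it drops patients without a 6-month value.** The article does not say how missing outcomes are handled, and a plain analysis of covariance would drop the same patients.
- **Every secondary outcome should be adjusted for its baseline.** The accelerometer is handed out before the envelope but worn for 7 days, so baseline activity appears to be recorded after allocation can be known.

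The objection does not show that the unadjusted test is the better choice. An analysis plan that is not shown does not remove the point either, because the article itself names the test.

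**Conclusion.** The point holds as a matter of efficiency. The article fixes an unadjusted test for its primary outcome although a suitable baseline covariate is collected. The result would not be invalid, and the trial is not underpowered by its own assumptions: 79% against a planned 80%.

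The loss is about 2 to 20% of the standard error, or about 2 to 14 percentage points of power, over assumed correlations of 0.2 to 0.6. In addition, the unadjusted estimate keeps a chance shift of up to about 1.7 to 2.8 points at correlations of 0.3 to 0.5. The conclusion rests on the article's SD of 15 and difference of 8, the assumed correlations, an assumed baseline SD of 15 for the imbalance figure, and the reading that the baseline ODI is completed before the envelope is opened. The change should be made, but it is not a condition for the trial's validity.

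**What to change.** Name a single primary analysis: the between-group difference in ODI at 6 months, adjusted for the ODI recorded 8 to 12 weeks before surgery. The assessment 1 week before surgery follows the intervention sessions and must not serve as the baseline covariate.

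The preferred route is the mixed model already planned, with baseline ODI as covariate, visit as a categorical factor and group-by-visit terms, and the 6-month contrast read from it. This also uses patients who miss the 6-month visit but have other post-baseline data. Analysis of covariance is the alternative, but it uses only patients with a 6-month value. Keep the two-sample t-test as a sensitivity analysis.

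Apply the same adjustment to secondary outcomes only where the baseline value is measured before allocation is revealed. For the 7-day accelerometer record this is not clear and should be settled first.

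The cost is a sentence or two in the Effect evaluation section, written before outcome data are analysed by arm. It needs no new measurements and no extra patients.

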### Hypotheses

Patients who receive PREPARE – a physiotherapeutic person-centred prehabilitation program based on a cognitive behavioural approach – before spinal fusion surgery will experience decreased disability levels, improved functioning, increased physical activity level, better health-related quality of life, decreased leg and back pain intensity, less pain catastrophizing, less pain-related fear, increased self-efficacy to exercise and less depressed mood after surgery compared to patients who receive conventional care. We further hypothesise that the between-groups difference will be largest at 6 months after surgery.Compared to those in the control group, patients who receive PREPARE will show a more rapid increase in their physical activity level measured objectively with an accelerometer at 3 and 6 months after surgery.From a societal perspective, PREPARE will be more cost-effective and show higher cost-utilities compared to conventional care at one year after surgery.

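### The random-intercept mixed model, on its ordinary reading, assumes one variance and one correlation across surgery and up to 5 years, so its standard errors for between-visit contrasts are likely to be wrong

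*Protocol article*

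**What the plan says.** The Effect evaluation section of the protocol article names one model for repeated measurements: "Since this trial will include repeated measures at different time-points, we will use a linear mixed model with random intercept". It mentions no random slope, residual covariance structure, visit-specific variance or robust standard error, and it does not say which visits enter.

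The Data collection section gives the schedule for patient-reported outcomes. Two visits precede surgery: "at baseline (8–12 weeks before surgery), at 1 week before surgery". Seven follow it: "at 3 weeks, 8 weeks, 3 months, 6 months, 1 year, 2 years and 5 years after surgery". That is nine visits in all.

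The same Effect evaluation section places the named analysis at one time-point, "for ODI at 6 months and all secondary outcomes at 6 months", with a two-sample t-test or Wilcoxon rank sum test between the groups. The Hypotheses section adds an expectation about time: "We further hypothesise that the between-groups difference will be largest at 6 months after surgery".

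**The concern.** A random intercept with independent, equal-variance residuals implies compound symmetry. Two ODI scores taken 7 to 11 weeks apart before surgery are then treated as no more alike than a pre-operative score and one taken 5 years after a fusion. Surgery lies between the second and third visits, and the gaps between visits range from weeks to years, so a single correlation is hard to defend.

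The model averages the variances and correlations and uses the averages for every contrast. If correlation is lower across surgery and over long intervals, the standard error comes out too small for changes that cross surgery and too large for the change between the two pre-operative visits. Such contrasts matter here, because the protocol expects the group difference to vary over time and to peak at 6 months. Any repeated-measures test of that pattern would not keep its nominal 5% error.

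**Working it through.** **The plan's own figure.** The Sample size section gives "80 % power, alpha = 0.05", a difference of 8 ODI points, SD 15 and 55 patients per group. Two-sided normal approximation: n = 2 × (1.960 + 0.842)² × 15² / 8² = 55.2, so 56 per group; power at 55 is 79.9%. The stated 55 is reproduced to within one patient. The SD of 15 is the only variability figure in the article, and no correlation is given.

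**Inputs to the check.** From the article: 55 per group, SD 15 and the nine visit times. Assumed: baseline 10 weeks before surgery (middle of the 8–12 week window); correlation 0.8 for two visits on the same side of surgery and 0.45 for two visits on opposite sides, each multiplied by exp(−0.003 × weeks apart); constant SD; complete data; a separate mean for each group at each visit.

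**Formulas.** With balanced complete data the random-intercept fit estimates the mean of the true variances and r̄, the mean of the true pairwise correlations. For the group difference in change from baseline to visit j, where r₀ⱼ is the true correlation and SD is constant:

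- Model SE = √[2 × 225 × (1 − r̄) × 2/55]
- True SE = √[2 × 225 × (1 − r₀ⱼ) × 2/55]
- Ratio = √[(1 − r̄)/(1 − r₀ⱼ)]
- Actual two-sided type I error at nominal 5% = 2Φ(−1.96 × ratio)

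**Results with all nine visits (r̄ = 0.529).**

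| Change from baseline to | r₀ⱼ | Model SE | True SE | Ratio | Type I error |
|---|---|---|---|---|---|
| 1 week before surgery | 0.779 | 2.78 | 1.90 | 1.46 | 0.4% |
| 6 months | 0.404 | 2.78 | 3.12 | 0.89 | 8.1% |
| 60 months | 0.200 | 2.78 | 3.62 | 0.77 | 13.3% |

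**Results with fewer visits.** With the six visits up to 6 months, r̄ = 0.588. The 6-month ratio is √(0.412/0.596) = 0.83 (error about 10%), and the pre-surgery ratio is √(0.412/0.221) = 1.37. With the seven visits up to 12 months the 6-month ratio is again 0.83. Dropping the late visits does not remove the problem.

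**Other assumed structures, nine visits.**

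- Equal correlation of 0.5 and constant SD: ratio 1.00 at every visit. In 4,000 simulated trials the error was 4.9 to 5.3%.
- First-order autoregressive in visit order, adjacent correlation 0.7 to 0.9: ratio 0.87 to 0.83 for the 6-month change, 0.81 to 0.70 for the 5-year change and 1.44 to 1.68 for the pre-surgery change. At 0.8, simulated errors were 10%, 12% and 0.25% respectively.
- Pre/post block (0.8 within pre, 0.7 within post, 0.3 across): ratio 0.80 for every post-surgery change (error 11.5%).
- Equal correlation of 0.5 with SD rising from 12 to 18: change contrasts run from 1.30 (pre-surgery) to 0.98 (5 years). Here variance drift alone makes most change contrasts conservative.

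**Group difference at a single visit.** With constant SD and complete data, model and true SE are both 15 × √(2/55) = 2.86, a ratio of exactly 1.00 at every visit. It departs from 1.00 only if the SD differs by visit: with the assumed rise from 12 to 18 and equal correlation it is 0.96 at 6 months and 0.85 at 5 years.

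**The case against.** The strongest reply is that the article names a random effect and is silent on the residual covariance. A random intercept can be combined with a structured residual, and such detail is commonly left to an analysis plan, which is not shown. This stands in part: the article does not say that the random intercept is the only covariance element. But it states a specific model rather than leaving one open, and the ordinary reading of that model is compound symmetry. Replacing a stated choice is different from filling a gap.

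A second reply is that the article does not say the model spans nine visits. This also stands. Recruitment runs to December 2016 and results are expected at the end of 2017, so a first report could not hold complete 2- or 5-year data. The 60-month figure therefore applies only if that visit is modelled. The 6-month figure does not depend on it.

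A reader might infer that the 6-month ODI comparison is itself compromised. The article does not support that: this comparison is assigned a two-sample t-test, which uses that visit's own variance. Physical activity at 3 and 6 months also has its own t-test. A reader might likewise infer that the standard errors are certain to be wrong, or always too small. Neither follows: they are right under exchangeability, and the direction differs by contrast and by structure.

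Finally, an unstructured covariance over nine visits is demanding for 110 patients. That is a fair reason to fix a fallback.

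**Conclusion.** The point holds for the supporting longitudinal analysis, as a likely rather than a certain error. If correlation falls across surgery and over time, the random-intercept model understates the standard error of the 6-month change by about 11 to 17% (error about 8 to 10% instead of 5%) and of the 60-month change, if modelled, by about 23% (error about 13%). It overstates that of the pre-surgery change by about 40 to 50%. These sizes rest on assumed correlations, constant SD 15 and complete data. Decaying and block structures agree in direction and rough size; an exchangeable structure gives no error. The t-test of ODI at 6 months is untouched, and so, with constant SD and complete data, are the model's single-visit group differences. The change is worth making, but the planned 6-month group comparison does not depend on it.

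**What to change.** In the Effect evaluation section, replace the random-intercept specification with a model that has visit as a categorical factor, group-by-visit terms and an unstructured residual covariance, fitted over the visits included in the report concerned. Name those visits and the group-by-visit contrast of interest. Fix the fallback in advance if the model does not converge: a heterogeneous first-order autoregressive or Toeplitz structure, or robust standard errors. Check that the chosen options can be run in the named software, SPSS 22.

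The cost is a sentence or two of text and more covariance parameters: 6 × 7/2 = 21 for the six visits up to 6 months and 9 × 10/2 = 45 for all nine, with 110 patients and likely losses over 5 years. The fallback may therefore be needed for the long-term report. Sample size, visits and the 6-month t-test do not change.

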#### Health economics

For our health economic analysis, a societal viewpoint will be used. Indirect and direct healthcare costs will be measured using a self-reported custom-made health economic questionnaire. Days of hospital stay will be determined from patient charts. Intervention costs will be calculated for each patient – including the number and duration of treatments for the 55 patients who will receive PREPARE. We will compare the mean total costs between the therapy groups. The cost prices of medical consumption will be calculated. All costs will be presented in euros. The human capital approach will be used to calculate productivity costs.

We will use these data to perform a cost-effectiveness analysis and cost-utility analysis. For the cost-effectiveness analysis, an incremental cost-effectiveness ratio (ICER) will be calculated, weighing total costs against disability levels (ODI). For the cost-utility analysis, utility will be calculated from EQ-5D scores for every assessment. Mean total costs will be weighed against mean health utility, i.e. comparing cost per Quality Adjusted Life Years (QALY) gained.

